### 3.2.3 Setting

Case scenarios will be completed at IDI. The observation of clinical practice will occur at the facility where the trainee works. See Section 3.1.3 for a list of the site selection criteria.

### 3.2.4 Population

Participants will be MLP who enroll in the Core IDT. Calculations of the number of participants required were based on the average scores of the pretest (42%) and post test (62%) for the Comprehensive HIV Care Including ART course during 12 separate occasions when it was taught at IDI. The standard deviation of scores for all participants was .11. The standard deviation of scores within groups at each occasion when the course was taught was .12 and the correlation between before and after test scores within a group was 0.5.

There are two approaches to considering sample size here, both of which are simplified versions of the analysis. The first is a single sample of individuals, who are tested before and after the three-week Core IDT. Participants from phase 1 and phase 2 sites are not expected to differ, because OSS has not started at the Phase 1 sites. A sample size of 13 would be needed to detect a change in average test score from .4 (pretest) to .5 (post test).

The second is a comparison of two groups: participants from phase 1 site and participants from phase 2 sites. At the end of the nine-month after IDT, participants from the phase 1 sites will have also benefited from OSS and their scores would increase more than participants from phase 2 sites. Each group has an average before test score (either pretest or after the three-week Core IDT) and an average nine-month test score and hence an average of differences in scores between before and nine-months. The effect will be the difference in average differences between the groups. A sample size of 23 participants in each group would be needed to detect a difference in change in scores of .1.

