### 3.2.2 Design

The alternative hypothesis that IDT has a significant effect on trainee competence and practice will be tested with a before/after comparison. The indicators of infectious disease competencies at baseline will be compared to those measures at the end of each session of the IDT core and booster courses. The indicators will be used to establish an acceptable standard, and we will test for differences in the percentage of MLP who meet the standard between baseline and subsequent measures. In regression analysis, we will adjust for unobserved differences across MLP using a random effects model and the *xtgee* command in Stata version 10. We will also compare change in competence between Arms A and B to test the incremental impact of OSS

on the proportion of MLP who meet the standards.

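### The Phase 1 v Phase 2 comparison of trainee competence leaves its starting score open between two pre-OSS scores, and a raw change from either is less precise than adjusting for both

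*Protocol*

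**What the plan says.** Section 3.2.1 has each trainee assessed three times: before the course, after the three-week session, and after the nine-month programme. Section 3.2.2 describes an uncontrolled before/after test of the training and then adds the arm comparison: "We will also compare change in competence between Arms A and B to test the incremental impact of OSS". That sentence goes on to give the outcome as the share of practitioners reaching the standard. It does not say from which earlier assessment change is counted. I read Arms A and B as Phase 1 and Phase 2.

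Section 3.2.4 describes the same comparison on mean scores: "Each group has an average before test score (either pretest or after the three-week Core IDT) and an average nine-month test score". It then fixes the measure: "The effect will be the difference in average differences between the groups". On size: "A sample size of 23 participants in each group would be needed to detect a difference in change in scores of .1". About the first two assessments it says: "Participants from phase 1 and phase 2 sites are not expected to differ, because OSS has not started at the Phase 1 sites".

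For the site-level indicators, section 3.3.2 does commit to one form: a regression of the nine-month indicator on Phase with the baseline value as covariate.

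**The concern.** Two starting scores are named for one effect and nothing in the protocol picks between them. Both precede OSS for trainees enrolled at the outset, so each change contrast estimates the same quantity from partly different data. An analyst could defend either one, and could do so after seeing which looks better.

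The change score is also a weak use of the data. At a before/after correlation of 0.5 it has the same variance as ignoring the earlier score altogether, although two informative earlier scores are collected on every trainee. What is at stake is the precision and credibility of the statement that OSS adds to individual competence beyond classroom training.

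**Working it through.** **Inputs.** From section 3.2.4: "The standard deviation of scores within groups at each occasion when the course was taught was .12"; "The standard deviation of scores for all participants was .11"; "the correlation between before and after test scores within a group was 0.5". From section 3.2.4 also 72 trainees, two per site, so 36 per arm. Alpha .05 and power 80% are stated only for the site-level calculation in section 3.3.4 and are borrowed here, two-sided. Only one correlation is given, so I assume r = 0.5 for all three pairs of scores and then vary it. Clustering within site is ignored at this step, and all figures are for mean scores.

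**The plan's own figure.** SD of change = .12 × √(2(1 − 0.5)) = .12. Then n = 2 × (1.960 + 0.842)² × (.12/.10)² = 22.6, so 23 per group, as stated. The figure alone does not identify the method: adjusting for one earlier score at 90% power also gives 23. The text, however, defines the effect as a difference of mean changes, and 80% is the only power that the protocol states as a design target.

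**Residual variance, in units of the score variance.**
- Change from either score: 2(1 − r) = 1.00
- Adjusting for one earlier score: 1 − r² = 0.75
- Adjusting for both: 1 − 2r²/(1 + r) = 1 − 0.5/1.5 = 0.67

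**Standard errors at 36 per arm.** Change: .12 × √(2 × 1.00/36) = .0283. Both adjusted: .12 × √(2 × 0.667/36) = .0231.

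**Power at 36 per arm**, Φ(difference/SE − 1.96), and how often the two change contrasts differ on significance (simulated):

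| True difference | Change score | Both adjusted | Two change contrasts disagree |
|---|---|---|---|
| .10 (design value) | 94% | 99% | 8% |
| .05 | 42% | 58% | 33% |

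A simulation with t-based tests gives 56% rather than 58% for the adjusted analysis at .05.

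**Trying both contrasts.** Covariance of the two change scores = 1 − .5 − .5 + .5 = .5, so their correlation is .5/1.00 = .5. From the bivariate normal, the chance under no effect that at least one passes two-sided .05 is 9.1%.

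**Sensitivity to the assumed correlations.** The either-significant rate stays between 8.6% and 9.5% over the sets tried. The variance ratio (both adjusted to change) is 0.62 to 0.72 for equal correlations of 0.3 to 0.8, and 0.35 to 0.87 for the unequal sets. In a random search over valid correlation matrices with equal variances, neither change score ever had the lower residual variance. Two extra covariates cost about (72 − 2 − 1)/(72 − 4 − 1) = 1.03, or 3% of variance.

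**The case against.** The open choice sits in sample-size text that calls its calculations simplified forms of the analysis, and it can be read as saying that 23 per group serves for either starting score. Section 3.2.2 plans a random-effects regression and speaks of baseline against later measures, which makes the pretest the natural reference. None of the listed hypotheses is the OSS effect on individual trainees, and the choice between change scores and covariate adjustment is often left to an analysis plan.

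Much of this stands. A reader might infer that the protocol will test both contrasts at .05, or that its false-positive rate is 9%. It says neither; the 9% applies only if both are tried or the better one is reported. A reader might also infer that the comparison is underpowered or that 23 is wrong. It is not: 23 reproduces, and at 36 per arm and a .1 difference power is already about 94% and the two contrasts disagree in only about 8% of trials. The figures are for mean scores, whereas section 3.2.2 names a proportion, for which nothing was computed.

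What does not stand is that the text settles the matter. The baseline wording in section 3.2.2 belongs to the uncontrolled test, the regression sentence does not say how the two earlier scores enter the arm contrast, and section 3.2.4 goes beyond silence by naming two alternatives.

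Two further objections bear on the remedy. Section 3.2.6 adds a training session midway through Phase 1 for replacements, whose earlier scores may follow the start of OSS at Phase 1 sites. And trainees come in pairs from randomised sites: with an assumed residual intraclass correlation of 0.1 to 0.3 (not in the protocol), variance is inflated 1.1 to 1.3 times, and a nominal 5% test that ignores site would run at about 6% to 9%. Any replacement analysis must deal with both.

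**Conclusion.** The point holds as an unfixed and inefficient contrast in a secondary comparison. It is not bias: for trainees enrolled at the outset both starting scores precede OSS. Nor does it touch the site-level OSS hypotheses.

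Adjusting for both earlier scores removes a third of the residual variance of a change score if all correlations equal 0.5; adjusting for one already removes a quarter. The direction does not depend on that assumption, apart from the small degrees-of-freedom cost, but the size does. At the design difference the practical gain is small. It matters if the true OSS effect is nearer .05, where the choice of starting score would change the verdict in about a third of trials.

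**What to change.** In sections 3.2.2 and 3.2.4, name one deciding arm comparison: a regression of the nine-month outcome on Phase, with the pretest and post-three-week scores as covariates and standard errors that allow for two trainees per site. Apply it to the case-scenario score used for the sample size, and use the corresponding covariate-adjusted model for the planned proportion meeting the standard. Report change-score comparisons as descriptive only.

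For replacements who join midway through Phase 1, do not treat scores taken after OSS began at their site as pre-OSS covariates. Restrict the main comparison to trainees enrolled at the outset and bring replacements into a sensitivity analysis.

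The cost is wording, since both scores are already collected, plus about 3% of variance in degrees of freedom and a stated rule for a trainee who lacks one of the earlier scores. The approach matches the baseline-adjusted regression that section 3.3.2 already uses for sites.

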### Based on IDI’s experience with the Joint Uganda Malaria Training Program (JUMP), the Core IDT was designed for two participants from each site. As explained in Section 3.3.4 with the sample size calculations for the facility cost and performance indicators, a sample size of 18 sites per treatment group or total of 36 sites was required. Consequently 72 participants would attend the Core IDT course. The evaluation is adequately powered to assess changes in case scenario scores, particularly as we have observed changes of double the magnitude that were used in the sample size calculations.

###

### 3.2.5 Ethical Considerations

**Consent**

Each trainee will apply to the IDI. The application form has two parts: a) course application, and b) consent to share the trainees’ data with the IDCAP evaluation. For the consent form, permission is requested to use trainee data to create a confidential record that will be used for the IDCAP evaluation. As stated on the form, “The decision is voluntary. You should feel completely free to choose not to share the data and to withdraw your data from the analysis without giving a reason.”

During the two days of clinical observation, a representative at each site and an IDCAP clinician will introduce the activity to the patients in the waiting room. Patients will be asked to give verbal consent to participate. The patient data will be anonymous, and the verbal consent process will preserve their anonymity. If the clinic staff need to distinguish patients who consent from other, the former will receive a card at the registration desk to show their decision. (Please see the script for introducing the clinical assessment.)

At the beginning of the consultation, the trainee will introduce the IDCAP clinician to the patients who gave verbal consent. The IDCAP clinician will explain to the patient that two clinicians will be routinely conferring about every patient. The patient should not be alarmed that the discussion could reflect severe or unusual illness. The IDCAP clinician will remind the patient that s/he has a right for the observation to stop at any time.

**Data Storage**

Please note that the IDCAP employees sign a confidentiality agreement as a condition of their employment at IDI.

The case scenarios will be completed at IDI and trainee scores will be reported in the IDI training data base as part of IDI’s monitoring and evaluation practices. Each trainee will be assigned a trainee ID number and s/he will be identified by it in the IDI training data base. The written responses will be stored in a locked file cabinet at the IDCAP office. The records of trainees who agree to share a confidential record will be assigned a second IDCAP number. The record will not contain the trainee’s name or demographic information that would identify him/her. The record will have an IDCAP number, and a confidential key will link the IDCAP number to the IDI training records. The confidential key will be stored securely and only the people listed on the consent form will have access to it.

The clinical observation will be performed by an IDCAP clinician who will spend two days at the trainee’s health facility observing a trainee’s clinical practice with seven patients in the outpatient clinic and seven patients in the HIV/AIDS clinic. The data collected by the IDCAP observer will be used to score the trainee’s clinical performance using a score sheet. The observation data will be identified by the trainee’s ID number in the data base. The IDCAP clinician will record anonymous data on patient history, physical examination, and laboratory investigations and other imaging in order to assess the quality of the trainee’s clinical practice. No identifying information about the patient will be recorded.

Each of the mobile teams who observe the trainees will travel with a small, locked box in which to store the observation score sheet and anonymous patient data when traveling. Written information will be stored in a locked file cabinet at the IDCAP office. The records of trainees who agree to share a confidential record will be assigned same IDCAP number and the data will be managed in the same way as the case scenarios with one exception. For the end-of-intervention assessment of outpatients, the principal investigator will transport the clinical assessment forms to Seattle WA for coding, where they will be stored in a locked file cabinet in her office, and then returned to the IDCAP office for data entry.

**Patient Safety**

If an emergency case is identified by the clinic team or the IDCAP clinician during the clinical observation of the trainee, the IDCAP clinician will stop the observation, support the trainee in the management of the emergency patient, and thereafter complete the Emergency Case Reporting Form.

### 3.2.6 Limitations

The success of the proposed intervention will depend on our ability to integrate it within other existing training activities, to avoid duplication of the considerable efforts to date. The diversity of training providers in Uganda is substantial, and coordination of those efforts must happen from within the Ugandan government. IDI is well positioned to facilitate this effort for IDT, as it has effectively worked with the MOH to have the Joint Uganda Malaria Training Program approved by the National Malaria Control Program and the National Malaria Case Management Technical Working Group. Many organizations have made major contributions to the body of training materials and learning approaches, and we intend to work closely with those partners to ensure our collective success. Most importantly, the WHO has established training materials that all parties view as essential and complementary, and working to ensure that this program builds on that foundation will be a high priority.

Another possible limitation would be attrition of the health professionals who have been trained. In collaboration with the Ministry of Health (MOH), IDCAP has built-in mechanisms to increase retention in the evaluation sites and institutionalize the quality improvements.

1. The district health officers have been asked to refrain from transferring the trainees in the core Infectious Disease Training (IDT) for 12 months and preferably 24 months after attending the IDT.
2. IDT trainees may be motivated to stay at the IDCAP sites until they complete the nine-month IDT, because they will benefit from distance learning and booster sessions at IDI as well as receiving an IDI certificate. In addition, the MOH’s Director of Clinical Services has encouraged IDI to make the IDT a degree program at Makerere University. Although creating a degree program will take longer than nine months, there is a precedent for awarding a degree retroactively. Participants in Hospice Uganda’s nine-month, palliative care course were awarded a degree retroactively when the course became a degree program.
3. Based on the SOMREC’s comments, IDI has decided to offer a fifth session of the IDT mid-way through phase 1. At sites where the IDT trainees have transferred or otherwise left, a replacement will be identified to attend this additional session.
4. Whereas the IDT will target a small number of staff in each facility, the on-site support seeks to institutionalize better clinical skills and quality improvement. The on-site support focuses on health professionals who are actively providing care at the site, which the IDCAP site assessment shows are the people with longer job tenure. When the practices are adopted by the team at the site, they can be shared as part of the orientation of new staff so that the skills and processes are effectively transferred.

# 3.3 Facility Cost and Performance Indicators

### 3.3.1 Methods

The second set of research question are: Does OSS, significantly improve clinic performance and health outcomes? If yes, are the OSS activities cost-effective? To answer these questions, 36 sites will receive the OSS activities for nine months, but 18 will be randomly assigned to receive the OSS in phase 1 and the others will be phase 2 sites that will serve as a control group in phase 1 and receive OSS months later. The unit of analysis will be the site, and the evaluation design is a randomized trial of sites on key performance indicators.

These research questions are reflected in specific objectives 2-5:

1. To evaluate the effectiveness of on-site support services in improving clinic performance
2. Estimate the cost-effectiveness of on-site support services
3. Compare two methods for estimating cost-effectiveness: a) economic modeling in which effectiveness is measured by original data on performance indicators at 36 sites and published estimates of the effect of the performance indicators on Disability Adjusted Life Years (DALYS), and b) estimates in which effectiveness is measured original verbal autopsy data on mortality among children five years or less.

5. Evaluate the effectiveness of bi-monthly OSS for six months on clinical performance at Phase 1 sites after monthly OSS for nine months during Phase 1.

For specific objectives 2 and 5, sites will be evaluated on the basis of a series of laboratory and clinical performance indicators for infectious diseases on the following areas: 1) preventing maternal to child transmission, 2) general HIV Care, 3) ART, 4) TB, 5) malaria, 6) emergency treatment and triage as presented in Table 1.

The laboratory performance indicators will be based on external quality assurance (EQA) data from three sources:

- National Tuberculosis Reference Laboratory data on acid-fast bacilli (AFB) smears for all IDCAP sites from Oct 2009 to present
- Uganda Virus Research Institute (UVRI) dry tube samples for HIV rapid test (3 positive and 3 negative per site) to test HIV panel proficiency
- Label and collect the 1st negative malaria blood smear and last positive smear each day for one month at every site.  Mobile team lab technicians will check the labels against the lab register to confirm they are the 1st negative and last positive.

The clinical performance indicators will be based on Health Management Information System (HMIS) data or field-tested alternatives to the HMIS forms. For example, the Uganda Malaria Surveillance Program (UMSP) patient visit form will replace the medical form 5. In addition to the UMSP forms, data will be extracted from the Antenatal Care Register, Maternity Register, Post Natal Care Register, Inpatient Register, HIV/ART cards, and TB Registers, and the laboratories’ Dried Blood Spot, Polymerase Chain Reaction DBS-PCR register .

The patient visit form (or modified version of it) would be completed by the health facility staff for every patient who visits the outpatient department. The form identifies patients by their name and outpatient department number. For most records, the data base will be anonymous in the sense that the names will not be entered into the data base and the patient records will not be linked across visits. For records that involve follow-up such as a referral or initiation of TB, the data will be confidential in the sense that names will be entered in the data base so that the information can be linked to records at the referral institution or the TB registers.

For the registers and HIV/ART cards, records will be checked for accuracy and completeness and individual data will be extracted at regular intervals. The records will be confidential in the sense that identifying information will be entered in the data base so that records can be linked between registers and cards, and individuals who are lost-to-follow-up can be traced.

All of these data are routinely collected and analyzed by the UMSP at Makerere Unversity or the Ministry of Health’s Quality of Care Initiative (QCI) without undergoing human subjects/ethics review. The IDCAP evaluation is similar to other activities that seek to improve the quality of care to meet existing Ministry of Health guidelines rather than to test new procedures or medical devices.

For specific objective 4, cost-effectiveness will be estimated with two methods. The first method is a model that combines original data on the performance indicators described in Table 1 at 36 sites and the cost of the capacity-building programs with published estimates of the cost of treatment and DALYs saved. The second method is based on original data on mortality of children under five years as described in Section 3.4 below, instead of performance indicators and DALYs. In other words, the denominator of the incremental cost effectiveness ratio will be measured two ways: economic modeling in which effectiveness is measured by original data on performance indicators and published estimates of the effect of the performance indicators on DALYS, and b) estimates in which effectiveness is measured with original verbal autopsy data on mortality.

The first method was proposed by Mason et. al. to estimate “policy-cost-effectiveness.”[[19]](#endnote-20) Their method grew out of observation that many cost-effective treatments were not adopted by providers. For example, the cost-effectiveness of co-trimoxazole prophalaxis is well established. Pitter et. al estimated that providing it to all HIV-infected people is cost-saving ($2.5 per person year) and providing it only to people in WHO clinical stages 2, 3, and 4 cost $22.23 per DALY gained relative to no prophalaxis.[[20]](#endnote-21) Yazdanpanah et.al. estimated that providing it to people in WHO clinical stages 2, 3, and 4 cost $150 per life year saved relative to no prophalaxis.[[21]](#endnote-22) This evaluation does not seek to replicate the cost-effectiveness analysis of this treatment. It evaluates the cost-effectiveness of a capacity-building intervention that promotes the adoption of the treatment at health facilities.

Interventions such as training and CQI are necessary for providers to adopt a treatment, and also involve costs and varying degrees of effectiveness. Mason et. al.’s method combines published estimates of the cost-effectiveness of the treatment with original research on the cost and effectiveness of interventions that encourage providers to adopt them. Please see the example in Table 2 below. Part A simply repeats the Pitter et. al. calculation of the saving in cost for cotrimoxazole prophalaxis for all HIV-infected people cited above. Part B is a hypothetical comparison of the cost-effectiveness of two capacity-building interventions to promote the treatment. The total cost of the capacity-building intervention plus treatment is more than the treatment alone, and the combination is no longer cost saving. The cost of classroom training is lower that classroom training plus OSS, but so is the effectiveness. As shown in this example, the incremental cost-effectiveness ratio relative to no prophalaxsis is calculated and OSS is more cost-effective.

This method explicitly recognized that there are valid reasons why cost-effective treatments are not adopted and builds interventions that promote their adoption onto published estimates. Mason et. al. list several characteristics that improve “policy cost-effectiveness” that apply to this analysis: 1) lower cost of the capacity-building program, 2) longer duration of the effect of the capacity-building program, 3) greater increase in the number of patients who use the treatment, and 4) greater gain in quality adjusted life years or DALYs of the treatment.

Original data on the cost and effectiveness of the capacity-building intervention will be collected. Cost data (e.g. B1 in Table 2) are available from IDI’s cost-accounting system, URC financial records, and district and facility personnel records. Training costs will be analyzed as an investment and amortized over a time period that reflects changes in guidelines and staff turnover (3 to 5 years). The effectiveness of the capacity-building program at changing provider behaviour. (e.g. B3 in Table 2) will be estimated from the performance indicators described above.

| **Table 2. Sample calculations of the cost-effectiveness ratio of capacity-building programs for cotrimoxazole prophalaxis** | | | |
| --- | --- | --- | --- |
|  |  |  |  |
|  | **No prophalaxis** | **Cotrimoxazole prophalaxis for all HIV infected people** | |
| **A. Pitter et.al. estimates** |  |  | |
| A1. Net treatment cost | $49.19 | $46.69 | |
| A2. Number of DALYS lost | 0.13430 | 0.06861 | |
| A3. Incremental benefit, i.e.DALYS gained |  | 0.0657 = 0.13430 - 0.06861 | |
| A4. Incremental cost |  | -$2.5 = $46.69 - $49.19 | |
| A5. Incremental cost-effectiveness ratio |  | Cost saving | |
| **B. Estimates with capacity-building** |  | **Classroom training** | **Classroom training plus OSS** |
| B1. Training cost |  | $10 | $110 |
| B2. Net program cost with training |  | $56.69  = $46.69 + 10 | $156.69  = $46.69 + $110 |
| B3. Effectiveness of training program at changing provider behavior |  | 5% | 90% |
| B4. Incremental benefit, i.e. DALYS gained |  | 0.0033  = 0.0657 * 0.05 | 0.0591  = 0.0657 * 0.9 |
| B5. Incremental cost |  | $7.50 | $107.50 |
| B6. Incremental cost-effectiveness ratio |  | $2273  = $7.50 / 0.0033 | $1819  = $107.5 / 0.0591 |

